### 2.3 Tertiary (Exploratory) Objectives

To explore if sera markers related to D-alanine, L-alanine, D-serine, L-serine, glycine and glutamate change from baseline to endpoint in those on active treatment.

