## 6.1 Biomarkers

The Director of the National Institute of Mental Health ([name]) has recently urged that clinical trials in mental health need to be enriched for biomarkers related to the proposed “target” of the intervention. This will be achieved by collecting a 25ml blood sample via venipuncture at both baseline and final patient interviews. A portion of this sample will be used to assess the concentration of key analytes in the pathways related to sodium benzoate. D-amino acid oxidase is needed to catabolize (break down) D-alanine. D-alanine can be measured in sera with High Performance Liquid Chromatography HPLC. In addition; we can measure related species that could be altered by the intervention, including L-alanine, D- and L-serine, glycine and glutamate. The investigators have suitable equipment and laboratory skills to assess these molecules. Collecting these measures will allow us to assess if sodium benzoate impacts on these analytes in the peripheral blood.

The remainder of the blood sample will be stored indefinitely for future research. However, future studies involving the stored blood samples will require approval from a Human Research Ethics Committee. There is strong justification to explore the association between common variants in genes involved in the glutaminergic pathways (benzoate impacts on analytes that are involved in these systems). For example, the recently published study in Nature identified 108 loci linked to

586 risk of schizophrenia. Several of these are linked to genes in these same pathways that are  
587 related to the action of sodium benzoate. Of particular relevance to the current protocol, common  
588 variants in serine racemase (SRR) were significantly associated with an increased risk of  
589 schizophrenia – this enzyme is upstream of DAAO, and involved in the metabolism of serine. While  
590 the study of the current sample size will not have sufficient power to test the impact of common  
591 variants in these genes versus outcomes in this study (the effect sizes for all SNPs linked to  
592 schizophrenia are small, between 1.1 and 1.4), we wish to bank this material down for future  
593 collaborative studies. This feature of the study will be clearly outlined in the consent form, and  
594 participants will be informed that DNA and sera samples may be used in future years by national  

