**Table 1: Schedule of Visits and Assessments**

**Assessment schedule can vary plus or minus five days for operational convenience**

| Visit                                       | 0
Screening
Phase | 1
Baseline | 2 | 3 | 4 | 5 | 6 | 7 | 8 | 9 | 10 | 11 | 12 | 13 | 14 |
|---------------------------------------------|-------------------------|---------------|---|---|---|---|---|---|---|---|----|----|----|----|----|
| WEEK                                 |                         | 0             | 1 | 2 | 3 | 4 | 5 | 6 | 7 | 8 | 9  | 10 | 11 | 12 | 14 |
| Study medication period(12 weeks)    |                         |               |   |   |   |   |   |   |   |   |    |    |    |    |    |
| SCREENING AND CONSENT                |                         |               |   |   |   |   |   |   |   |   |    |    |    |    |    |
| Assessment of current medication            | X                       |               |   |   |   |   |   |   |   |   |    |    |    |    |    |
| Informed consent                            | X                       |               |   |   |   |   |   |   |   |   |    |    |    |    |    |
| Ongoing capacity                            |                         | X             | X | X | X | X | X | X | X | X | X  | X  | X  | X  |    |
| Inclusion / exclusion criteria              | X                       |               |   |   |   |   |   |   |   |   |    |    |    |    |    |
| Urine pregnancy test (females only)         | X                       |               |   |   |   |   |   |   |   |   |    |    |    |    |    |
| Drug dispensation (after randomisation)     |                         | X             |   | X |   | X |   | X |   | X |    | X  |    |    |    |
| SAFETY                               |                         |               |   |   |   |   |   |   |   |   |    |    |    |    |    |
| Adverse events                              |                         |               |   | X | X | X | X | X | X | X | X  | X  | X  | X  | X  |
| Physical health and metabolic measures      |                         | X             |   | X |   | X |   | X |   | X |    | X  |    | X  |    |
| EFFICACY                             |                         |               |   |   |   |   |   |   |   |   |    |    |    |    |    |
| PANSS TOTAL SCORE                           | X                       | X             |   | X |   | X |   | X |   | X |    | X  |    | X  |    |

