| GAF                                         |                         | X             |   | X |   | X |   | X |   | X |    | X  |    | X  |    |
| AQOL                                        |                         | X             |   | X |   | X |   | X |   | X |    | X  |    | X  |    |
| APQ-6                                       |                         | X             |   |   |   |   |   |   |   |   |    |    |    | X  |    |
| CGI                                         |                         | X             |   | X |   | X |   | X |   | X |    | X  |    | X  |    |
| HDRS                                        |                         | X             |   | X |   | X |   | X |   | X |    | X  |    | X  |    |
| PGI                                         |                         |               |   |   |   |   |   |   |   |   |    |    |    | X  |    |
| OTI                                         |                         | X             |   |   |   | X |   |   |   | X |    |    |    | X  |    |
| IPAQ                                        |                         | X             |   |   |   |   |   |   |   |   |    |    |    |    |    |
| SIMPAQ                                      |                         |               | X |   |   |   |   |   |   |   |    |    |    |    |    |
| PAQ                                         |                         |               |   | X |   |   |   |   |   |   |    |    |    |    |    |
| OTHER                                |                         |               |   |   |   |   |   |   |   |   |    |    |    |    |    |
| Drug compliance                             |                         |               | X | X | X | X | X | X | X | X | X  | X  | X  | X  |    |
| Blood test (DNA extraction, , sera storage) |                         | X             |   |   |   |   |   |   |   |   |    |    |    | X  |    |

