## **6.2 Study Procedures**

Dispensing of sodium benzoate to participants will occur once consent has been obtained and after the screening phase and randomisation has occurred. A delegated Research Pharmacist at the Princess Alexandra Hospital will dispense medication for all sites. For each randomised participant, the entire 12 weeks of study medication will be provided to QCMHR delegated research staff. The study medication will then be distributed to the participant on a fortnightly basis by delegated research staff in line with this protocol (section 7.4). There will be a total of 6 dispensations per participant.

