### **6.4.3 Pharmacokinetics**

The following information is sourced directly from the Concise International Chemical Assessment Document 26 "Benzoic Acid and Sodium Benzoate", World Health Organization.

After oral ingestion of benzoic acid and sodium benzoate, there is a rapid absorption (of undissociated benzoic acid) from the gastrointestinal tract in experimental animals or humans. One hundred percent absorption can be assumed from the general literature when sodium benzoate is administered orally. In humans, the peak plasma concentration is reached within 1–2 hours. In the acid conditions of the stomach, the equilibrium moves to the undissociated benzoic acid molecule, which is believed to be absorbed rapidly. Benzoate from sodium benzoate changes from the ionized form to the undissociated benzoic acid molecule. As a result, the metabolism and systemic/toxic effects of benzoic acid and sodium benzoate can be evaluated together.

After oral and dermal uptake, sodium benzoate is metabolized in the liver by conjugation with glycine, resulting in the formation of hippuric acid. The rate of biotransformation in humans is high: after oral doses of 40, 80 or 160 mg sodium benzoate/kg body weight, the transformation to hippuric acid was independent of the dose — about 17–29 mg/kg body weight per hour, corresponding to about 500 mg/kg body weight per day. Other authors obtained higher values of 0.8–2 g/kg body weight per day. Hippuric acid is rapidly excreted in urine. In humans, after oral doses of up to 160 mg/kg body weight, 75–100% of the applied dose is excreted as hippuric acid within 6 hours after administration, and the rest within 2–3 days.

The limiting factor in the biosynthesis of hippuric acid is the availability of glycine. The utilization of glycine in the detoxification of benzoate results in a reduction in the glycine level of the body. Therefore, the ingestion of benzoic acid or its salts affects any body function or metabolic process in which glycine is involved; for example, it leads to a reduction in creatinine, glutamine, urea, and uric acid levels.

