## **8.3 Time Period, Frequency, and Method of Detecting AEs and SAEs**

All adverse events will be recorded between the time of consent and the final visit (week 14), two weeks post final treatment. Each Participant will be monitored regularly by the investigator and study personnel for adverse events occurring throughout the study. The research assistant will enquire about AEs by asking the following non-leading questions:

At the first scheduled visit (pre-dosing) participants will be asked:

*"How are you feeling?"*

At subsequent scheduled visits, participants will be asked:

*"Since your last visit, have you had any health problems?"*

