| 6. | Home visits                                           | Participants may be seen at home rather than in the clinic.
Individuals with psychosis can often experience hallucinations and delusions which could result in unpredictable behaviour. | Possible | Minor-Moderate | Medium-High  | 
First preference should be interview conducted at the clinic in a suitable interview room.
 
Two staff will be required for home visits and will carry a mobile phone.
 
Research staff will adhere to a sign in/out policy and advise the Project Manager of the address they will be attending.
 
Any incidents from a home visit will be reported to the Project Manager and Chief Investigator and documented in the CRF or if required reported to Metro South HREC.
 |
| 7. | Transporting participants in QLD Health work vehicles | Research staff will be transporting participants to pathology appointments and may be required to transport participants to the interview site.
- There may be risk associated with     | Possible | Minor-Moderate | Medium -High | 
Research staff will have a current QLD Driver's Licence and completed the mandatory Driver Safety E-Learning Course.
 
Recruitment of experienced mental health clinicians who will be able to and manage
                                                                                                                                                                                                                                                                           |

|  |  |                                                                                                                                                                                     |  |  |  |                                                                                                                                                                                          |
|--|--|-------------------------------------------------------------------------------------------------------------------------------------------------------------------------------------|--|--|--|------------------------------------------------------------------------------------------------------------------------------------------------------------------------------------------|

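### The week-12 biomarker sample is not tied to dosing and may be drawn up to 5 days after study medication runs out, which could dilute the exploratory biomarker comparison

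*Protocol*

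**What the plan says.** **Objective.** Section 2.3, repeated as an endpoint in 11.2.3, asks whether serum D- and L-alanine, D- and L-serine, glycine and glutamate "change from baseline to endpoint in those on active treatment".

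**Sampling.** Section 6.1 provides for "collecting a 25ml blood sample via venipuncture at both baseline and final patient interviews". The Table 1 row "Blood test (DNA extraction, , sera storage" is marked at week 0 and week 12 and is blank at week 14. Table 1 also states: "Assessment schedule can vary plus or minus five days for operational convenience". The risk plan in 8.12 adds: "Research staff will be transporting participants to pathology appointments". No section gives an interval between the last capsule and the draw, or asks for either time to be recorded.

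**Supply.** Section 6.2: "There will be a total of 6 dispensations per participant". Table 1 places these at weeks 0, 2, 4, 6, 8 and 10, with none at week 12. The overdose item in 8.12 sets each at 14 days. Dosing is twice daily (7.4).

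**Pharmacokinetics.** Section 6.4.3: "In humans, the peak plasma concentration is reached within 1–2 hours". It puts excretion as hippuric acid at 75–100% of a dose within 6 hours and the remainder over 2–3 days, and cites up to 97% within 6 hours in healthy adults.

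**The concern.** The tertiary objective concerns change while participants are taking benzoate. Section 6.5 attributes the effect to the drug occupying the active site of DAAO, and 6.4.3 says that clearing the drug uses up glycine, one of the listed analytes. If the drug goes within hours to a few days, the time since the last capsule is a main determinant of what the sample can show. The schedule leaves that time open and centres the draw on the day the capsules run out.

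A participant who follows the protocol exactly can therefore give an endpoint sample several days off drug and still count as on active treatment. Mixing such samples with on-drug samples would, if the analytes follow the drug down, shrink the mean change and favour a finding of no change. A statistical analysis plan could not repair this afterwards, because it cannot recover a dose-to-draw interval that was neither controlled nor recorded.

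**Working it through.** **1. Supply, reproducing the protocol's figure.** 6 dispensations × 14 days = 84 days = 12 weeks, which agrees with section 6.2. At two capsules a day this is 84 × 2 = 168 capsules. With full adherence, a first capsule on the morning of day 0 puts the last on the evening of day 83. A first capsule on the evening of day 0 puts the last on the morning of day 84.

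**2. Draw date against end of supply.** Week 12 is day 84, and ±5 days gives day 79 to day 89. The difference from day 84 runs from 79 − 84 = −5 to 89 − 84 = +5 days. Counted from the last pack alone, with the week-10 and week-12 visits each moving by ±5 days, the range is −10 to +10 days. That wider range needs leftover capsules from earlier packs not to be used.

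**3. Share of draws, by assumption only.** The protocol gives no distribution of visit days. If the 11 permitted days were equally likely:

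| Draw day | Share |
|---|---|
| 79–83, before | 5/11 = 45% |
| 84 | 1/11 = 9% |
| 85–89, after | 5/11 = 45% |
| of which 87–89 | 3/11 = 27% |

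**4. Drug left at the draw.** Assume a constant fractional loss fixed by the 6-hour figures, so that remaining = (1 − f)^(t/6), with f the fraction excreted by 6 hours.

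| Hours since capsule | f = 0.75 | f = 0.97 |
|---|---|---|
| 6 | 25% | 3% |
| 12 | 0.25² = 6% | 0.03² = 0.1% |
| 24 | 0.25⁴ = 0.4% | below 0.001% |

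The stated 2–3 days for the remainder may mean a slower tail than this. Even so, by day 87 the protocol's own figures leave nothing from a last capsule on day 83 or 84.

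**5. What dilution could cost (illustration).** Suppose 66 active participants (the per-group number in 11.3), a two-sided 0.05 test of within-arm change, a standardised change δ, the effect wholly lost in a share p of samples, and an unchanged standard deviation. Then power ≈ Φ(δ(1 − p)√66 − 1.96), ignoring the negligible opposite tail except where power is near 5%.

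| p | δ = 0.5 | δ = 0.35 |
|---|---|---|
| 0 | 98% | 81% |
| 25% | 86% | 57% |
| 50% | 53% | 30% |
| 75% | 17% | 11% |

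Neither δ nor p comes from the protocol. The table shows only how sensitive the comparison would be if the effect vanished with the drug.

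**The case against.** The best reply is that the documents describe clearance of benzoate, not of the analytes. Section 1.2 presents the mechanism as accumulation of endogenous D-alanine. If that accumulation persists between doses, a draw 12 hours after a capsule is perfectly informative, and even a draw a day or two later may be. This stands. It means the loss cannot be sized from the documents, and that the concern rests mainly on draws made days after the last capsule.

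The same window also allows draws up to 5 days before supply ends, and missed doses leave capsules over. A reader might infer that the sample always falls at or after the end of supply, but the schedule does not say that.

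A reader might also infer a week-14 draw, because section 8.3 calls that visit "the final visit (week 14), two weeks post final treatment". Section 8.3 defines the adverse-event period, and Table 1 has no blood draw at week 14. The wording in 6.1 is loose, but the table settles the visit.

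It is tempting to ask for matched meals and time of day as well. No section says that these serum amino acids vary with either, and taking capsules with meals is only a dosing instruction, so that demand has no support here.

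Compliance is checked by self-report and capsule count at each visit (7.10), which gives some information on recent dosing, though no time of last capsule. A laboratory manual might set the timing, but the protocol refers to none. Finally, the objective is exploratory, and 6.1 lets participants decline sampling. Both limit the importance of the point without removing it.

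**Conclusion.** The point holds in a limited form. The endpoint sample is not tied to dosing, its nominal day is the day supply ends, and a fully adherent participant can be sampled up to 5 days later within protocol. On the protocol's own pharmacokinetics, some of those samples would be off drug. This could dilute the change examined in the tertiary objective.

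The size is unknown. It depends on the actual visit days and on how long the analyte changes outlast the drug, and the documents give neither. The 45% and 27% shares rest on equally likely visit days, and the power figures on assumed effects.

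A reader might conclude that the biomarker result will be a false null. The text supports only that it could be biased towards no change. Nor does section 6.1 say that the samples are there to explain a null PANSS result: it says only that trials should carry target-related biomarkers and that these measures show whether benzoate alters the analytes in peripheral blood. The primary PANSS analysis is not affected.

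**What to change.** - In 6.1, replace the reference to the final interview with the week-12 visit of Table 1.
- Within the existing window, schedule the draw on or before the participant's last day of study medication.
- Record in the CRF the date and clock time of the last capsule and of the draw.
- Prespecify an interval since the last capsule. Use samples inside it for the main biomarker comparison and report the others separately.

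The cost is four CRF entries (two dates, two times) and tighter booking of the pathology slot. With full adherence from day 0, the usable days shrink from 11 (days 79–89) to 5 or 6 (day 79 to day 83 or 84) for the blood draw only; the other week-12 assessments can keep the full window. Some samples will leave the main biomarker comparison. The retained set is selected after randomisation, so it should be described as such, and the same timing rule should apply to placebo samples if the arms are compared. No extra visit or blood is needed, and dose, supply and treatment duration are unchanged.

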**Table 1: Schedule of Visits and Assessments**

**Assessment schedule can vary plus or minus five days for operational convenience**

| Visit                                       | 0
Screening
Phase | 1
Baseline | 2 | 3 | 4 | 5 | 6 | 7 | 8 | 9 | 10 | 11 | 12 | 13 | 14 |
|---------------------------------------------|-------------------------|---------------|---|---|---|---|---|---|---|---|----|----|----|----|----|
| WEEK                                 |                         | 0             | 1 | 2 | 3 | 4 | 5 | 6 | 7 | 8 | 9  | 10 | 11 | 12 | 14 |
| Study medication period(12 weeks)    |                         |               |   |   |   |   |   |   |   |   |    |    |    |    |    |
| SCREENING AND CONSENT                |                         |               |   |   |   |   |   |   |   |   |    |    |    |    |    |
| Assessment of current medication            | X                       |               |   |   |   |   |   |   |   |   |    |    |    |    |    |
| Informed consent                            | X                       |               |   |   |   |   |   |   |   |   |    |    |    |    |    |
| Ongoing capacity                            |                         | X             | X | X | X | X | X | X | X | X | X  | X  | X  | X  |    |
| Inclusion / exclusion criteria              | X                       |               |   |   |   |   |   |   |   |   |    |    |    |    |    |
| Urine pregnancy test (females only)         | X                       |               |   |   |   |   |   |   |   |   |    |    |    |    |    |
| Drug dispensation (after randomisation)     |                         | X             |   | X |   | X |   | X |   | X |    | X  |    |    |    |
| SAFETY                               |                         |               |   |   |   |   |   |   |   |   |    |    |    |    |    |
| Adverse events                              |                         |               |   | X | X | X | X | X | X | X | X  | X  | X  | X  | X  |
| Physical health and metabolic measures      |                         | X             |   | X |   | X |   | X |   | X |    | X  |    | X  |    |
| EFFICACY                             |                         |               |   |   |   |   |   |   |   |   |    |    |    |    |    |
| PANSS TOTAL SCORE                           | X                       | X             |   | X |   | X |   | X |   | X |    | X  |    | X  |    |
| GAF                                         |                         | X             |   | X |   | X |   | X |   | X |    | X  |    | X  |    |
| AQOL                                        |                         | X             |   | X |   | X |   | X |   | X |    | X  |    | X  |    |
| APQ-6                                       |                         | X             |   |   |   |   |   |   |   |   |    |    |    | X  |    |
| CGI                                         |                         | X             |   | X |   | X |   | X |   | X |    | X  |    | X  |    |
| HDRS                                        |                         | X             |   | X |   | X |   | X |   | X |    | X  |    | X  |    |
| PGI                                         |                         |               |   |   |   |   |   |   |   |   |    |    |    | X  |    |
| OTI                                         |                         | X             |   |   |   | X |   |   |   | X |    |    |    | X  |    |
| IPAQ                                        |                         | X             |   |   |   |   |   |   |   |   |    |    |    |    |    |
| SIMPAQ                                      |                         |               | X |   |   |   |   |   |   |   |    |    |    |    |    |
| PAQ                                         |                         |               |   | X |   |   |   |   |   |   |    |    |    |    |    |
| OTHER                                |                         |               |   |   |   |   |   |   |   |   |    |    |    |    |    |
| Drug compliance                             |                         |               | X | X | X | X | X | X | X | X | X  | X  | X  | X  |    |
| Blood test (DNA extraction, , sera storage) |                         | X             |   |   |   |   |   |   |   |   |    |    |    | X  |    |

